# After-School to Pre-Sleep Energy Restriction for obesity in primary school children in grades 3–6: protocol for a parallel, randomized controlled trial

**DOI:** 10.1186/s13063-026-09785-2

**Published:** 2026-05-22

**Keywords:** Pediatric obesity, Eating behavior, Energy intake, Randomized controlled trial

## Abstract

**Background:**

The rising prevalence of childhood obesity has become a major global public health concern. Dietary intervention remains the cornerstone of pediatric obesity management. However, both conventional all-day energy-restricted diets and time-restricted eating have limitations in school-aged children. Studies indicate that excessive evening caloric intake is closely associated with obesity. This trial aims to evaluate the efficacy of an After-School to Pre-Sleep Energy Restriction (ASER) strategy compared with standard dietary intervention for pediatric obesity management.

**Methods and analysis:**

This study is a prospective, randomized, open-label, parallel-group trial. We plan to enroll 164 obese children from grades 3 to 6, who will be stratified by age, gender, and BMI *z*-score and randomly assigned in a 1:1 ratio to either the ASER group or the control group. The 24-week intervention consists of an intensive phase (weeks 0–12) followed by a maintenance phase (weeks 13–24). The primary endpoint is the between-group difference in BMI *z*-score (BMIz) change at week 12. Secondary endpoints include within-group BMIz changes at week 12; between-group and within-group BMIz changes at week 24; between-group and within-group changes in %BMI_95_, body composition, growth parameters, cardiometabolic markers, and psychobehavioral metrics at both 12 and 24 weeks; and between-group differences in the incidence of adverse events at weeks 12 and 24.

**Ethics and dissemination:**

This study was approved by the Medical Ethics Committee of the First Affiliated Hospital of Guangxi Medical University (Approval No.: 2025-K0254). Written informed consent will be obtained from legal guardians, and assent will be obtained from child participants prior to enrollment. Study findings will be published in peer-reviewed journals.

**Trial registration:**

The trial was prospectively registered on 3 September 2025, prior to the first participant enrollment, with the Chinese Clinical Trial Registry (ChiCTR2500108702). The URL of the specific trial registry record is https://www.chictr.org.cn/showproj.html?proj=275435.

## Introduction

The global epidemic of childhood and adolescent obesity continues to escalate. Data from the Non-Communicable Diseases Risk Factor Collaboration (NCD-RisC) reveal a substantial increase in the global age-standardized obesity prevalence among school-aged children and adolescents (5–19 years) from 1990 to 2022, with rates rising from 1.7% to 6.9% in girls and from 2.1% to 9.3% in boys [1]. This public health crisis has extended beyond concerns of physical appearance, contributing to metabolic comorbidities and increased incidences of depression and anxiety [2–4]. Notably, obesity phenotypes established before puberty may induce metabolic memory effects through epigenetic modifications, significantly elevating the risk of cardiovascular diseases in adulthood [5, 6]. Therefore, timely and effective interventions targeting childhood obesity are critical for improving long-term outcomes.

Regarding strategies for obesity management, although bariatric surgery and novel pharmacotherapies such as GLP-1 receptor agonists have demonstrated remarkable efficacy in adults [7–10], their application in pediatric populations remains limited, largely due to insufficient long-term safety data concerning growth trajectories (e.g., bone mineral density), neurocognitive development, and psychosocial adaptation, as well as disparities in healthcare accessibility arising from unequal regional medical resources and socioeconomic factors [11–13]. Consequently, early lifestyle interventions, particularly dietary modifications, remain the cornerstone of clinical practice guidelines for managing childhood obesity across different countries.

Energy-restriction regimens, including continuous energy restriction (CER), intermittent energy restriction (IER), and very low energy diets (VLEDs), have been shown to induce weight loss by reducing overall caloric intake [14–17]. However, there is insufficient evidence regarding the long-term safety of stringent daily energy restrictions—especially VLEDs—in pediatric populations [18]. In addition, practical barriers—such as the inability of school meal programs to accommodate individualized low-energy dietary needs, the limited self-regulatory capacity of children, and the lack of consistent parental supervision in dual-working families—make adherence to all-day energy restriction particularly challenging [19, 20].

On the other hand, time-restricted eating (TRE), an emerging chrono-nutrition strategy, has demonstrated distinct advantages in weight management and metabolic regulation [21]. Nonetheless, current evidence for TRE is primarily derived from adult populations, and its strict feeding windows (e.g., requiring cessation of intake by 16:00) are often incompatible with the daily schedules of school-aged children. Crucially, high-quality evidence regarding the long-term safety of stringent TRE protocols on children’s growth, development and psychosocial outcomes remains lacking [22]. Thus, both conventional all-day energy restriction and TRE approaches exhibit limitations in pediatric applications. Contemporary interventions should be developmentally appropriate and aligned with children's daily routines to facilitate sustainable behavior change. Interventions that minimize implementation barriers while accommodating educational schedules and family dynamics are urgently needed for pediatric obesity management in real-world settings.

Accumulating evidence suggests that excessive nighttime caloric intake is closely associated with obesity in both adults and children [23–32]. For example, Longo-Silva et al. observed that individuals consuming their largest meal at dinner had higher BMI and increased risk of obesity [23]. A systematic review and meta-analysis revealed that pre-sleep high-energy intake was associated with increased obesity risk in children and adolescents [29]. Moreover, Garaulet et al. reported diminished weight loss efficacy in obese individuals consuming most daily calories after 15:00 [31]. Mechanistically, nighttime eating may exacerbate metabolic risks through enhanced fat storage, suppressed lipid oxidation, elevated LDL and total cholesterol levels, amplified hunger signaling, and reduced energy expenditure [33, 34]. These findings suggest the evening-to-sleep period as a critical window for metabolic intervention. Interventions targeting nighttime energy surplus may represent a promising and feasible strategy for weight management in obese children. To date, however, we have not identified any randomized controlled trials specifically investigating nighttime caloric restriction, rather than complete fasting, in obese pediatric populations.

In summary, considering children’s growth trajectories, dietary patterns, and prior research evidence, this randomized controlled trial evaluates an intervention model, after-school to pre-sleep energy restriction (After-school Energy Restriction, ASER), in obese children in grades 3–6. ASER focuses on limiting energy intake during the critical window from after school (approximately 17:30) to bedtime, permitting controlled energy intake tailored to age-specific nutritional requirements, coinciding with the period of peak caloric surplus. Rather than enforcing absolute fasting, ASER requires moderated energy intake after school, thereby aligning better with local cultural practices and daily living habits, while minimizing the risk of undernutrition and other adverse effects. This approach may reduce the burden of familial supervision, enhance children’s adherence to the intervention, and ultimately optimize its effectiveness.

## Methods and analyses

### Study design

This study is a prospective, randomized, open-label, parallel-controlled trial to be conducted at the First Affiliated Hospital of Guangxi Medical University. A total of 164 eligible participants will be recruited from non-boarding public primary schools in urban areas of Nanning and randomized in a 1:1 ratio into either the ASER group or the standard dietary intervention group (control group).

Participants will first undergo an initial screening based on predefined inclusion and exclusion criteria, including assessments of medical history, current medication use, and anthropometric measurements. Written informed consent will be obtained from the participants’ guardians before any study-specific procedures are performed.

Following consent, baseline evaluations will be conducted, including the collection of sociodemographic information, lifestyle factors, results from an oral glucose tolerance test (OGTT), insulin release test, lipid profile, and body composition analysis. Eligibility will be reconfirmed based on evaluation results, after which, participants will be randomized.

The intervention will last for 24 weeks, consisting of an initial 12-week intensive intervention phase followed by a 12-week maintenance phase. Participants assigned to the ASER group will be required to strictly restrict energy intake during the evening-to-bedtime period (starting at 17:30), while having no specific restrictions during other periods, although adherence to healthy eating patterns will be encouraged. Participants in the control group will receive standard weight management counseling in accordance with the Nutritional Guidelines for Weight Management in School-Aged Children [35].

Throughout the study, both groups will receive additional lifestyle counseling beyond the dietary intervention, including recommendations on physical activity and sleep hygiene. The protocol has been developed following the SPIRIT 2013 statement (Standard Protocol Items: Recommendations for Interventional Trials) [36] (Fig. 1).

**Fig. 1 Fig1:**
[figure not shown]
SPIRIT schedule of enrollment, interventions, and assessments. “X” denotes the timepoints at which each data collection activity is performed. ASER, After-School to Pre-Sleep Energy Restriction (After-school Energy Restriction); OGTT, oral glucose tolerance test; IRT, insulin release test; HbA1c, glycated hemoglobin; CRP, C-reactive protein; IGF-1, insulin-like growth factor 1; ECG, electrocardiogram

### Sample size estimation

Assumptions were informed by prior pediatric studies [14, 37], together with clinical considerations. We anticipate a between-group difference of 0.14 in BMI *z*-score change (standard deviation = 0.28) after 12 weeks of intervention. Assuming a two-sided significance level of 0.05, a statistical power of 85% (1–β = 0.85), and an expected dropout rate of 20%, a total of 164 participants (82 per group) will be required.

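### With the stated inputs and 20% dropout, 164 children give about 81% power, not 85%; the other inputs lead to 164 only at about 10% dropout

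*Protocol article*

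**What the plan says.** The Sample size estimation section of the protocol article gives a complete set of inputs for the primary endpoint, the between-group difference in BMI z-score change at week 12:

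- Effect: "We anticipate a between-group difference of 0.14 in BMI" z-score change.
- Variability: "standard deviation = 0.28) after 12 weeks of intervention".
- Error rates: "Assuming a two-sided significance level of 0.05", with 85% power.
- Result: "an expected dropout rate of 20%, a total of 164 participants (82 per group) will be required".

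The total is repeated in the Abstract ("We plan to enroll 164 obese children from grades 3 to 6") and under Study design ("A total of 164 eligible participants will be recruited"), where allocation is 1:1. The section mentions no covariate adjustment, no baseline correlation and no gain from repeated measurements. It inflates for dropout in the ordinary way, which treats children who drop out as lost to the analysis.

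**The concern.** Every input is printed, so the total can be checked directly, and it comes out too small for the stated dropout. The shortfall is larger than rounding or the choice between a normal and a t-based formula can explain.

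The calculation justifies the number of children enrolled and sets the yardstick for the only primary endpoint. If the trial ends without a significant difference, readers will judge that result against a planned type II error of 15%. On the stated inputs the planned type II error is about 18% to 19%. Type I error, the estimates and their confidence intervals are not affected.

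**Working it through.** **Inputs** (Sample size estimation; allocation from Study design): difference Δ = 0.14; SD of change σ = 0.28; Δ/σ = 0.50; two-sided α = 0.05; power 0.85; dropout 20%; 1:1 allocation; stated total 164, or 82 per group.

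**Step 1. Evaluable children per group for 85% power.**

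Normal approximation: n = 2(z₀.₉₇₅ + z₀.₈₅)² / (Δ/σ)² = 2(1.960 + 1.036)² / 0.5² = 71.8, so 72.

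Two-sample t-test (noncentral t): n = 72.8, so 73.

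**Step 2. Attempt to reproduce 82 per group at 20% dropout.**

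| Inflation rule | From 72 | From 73 | Total |
|---|---|---|---|
| n / (1 − 0.20) | 90 | 91.25, so 92 | 180 or 184 |
| n × 1.20 (a common slip) | 86.4, so 87 | 87.6, so 88 | 174 or 176 |

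No entry gives 82 per group. Changing one other input at a time, with n / (1 − 0.20), does not give it either:

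- One-sided α: 58 evaluable, 73 after inflation, 146 in total.
- 80% power: 63 or 64 evaluable, 79 or 80 after inflation, 158 or 160 in total.
- 90% power: 85 or 86 evaluable, 107 or 108 after inflation, 214 or 216 in total.

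**Step 3. Dropout rate that does give 82.**

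- t-test: 73 / 0.90 = 81.1, so 82 per group and 164 in total.
- Normal approximation: 72 / 0.88 = 81.8, so 82 per group.

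With the other inputs as printed, 164 therefore corresponds to about 10% dropout by the t-test and about 12% by the normal approximation.

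**Step 4. Power with 164 randomised and 20% lost.**

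Evaluable per group: 82 × 0.80 = 65.6.

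Normal approximation: Φ(0.5 × √(65.6/2) − 1.960) = Φ(0.904) = 0.817.

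t-test: 0.811.

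With whole numbers of 65 or 66 per group, power is 80.8% to 81.4% (t-test) or 81.3% to 81.9% (normal).

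**Step 5. What 82 per group supports.**

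- Largest dropout that keeps 85% power: 1 − 72.8/82 = 11.2% (t-test), or 1 − 72/82 = 12.2% (normal).
- Difference detectable with 85% power at 65.6 per group: about 0.148 by the t-test, against 0.14 planned.
- Variance that covariates would have to explain to restore 85% at 65.6 per group: 1 − 65.6/71.8 = 8.7% by the normal approximation, and about 10% by the t-test.

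**The case against.** The strongest reply is that the primary analysis is not the unadjusted comparison behind the calculation. The Statistical analysis section specifies a mixed-effects model adjusted for age, sex and baseline BMI z-score. Under Intervention measures, anthropometry is also taken at weeks 4 and 8, so a child lost before week 12 may still contribute if those visits enter the model. Under Quality control and data management, the investigators undertake to seek outcome data from children who withdraw. Covariates explaining about 10% of the variance of change would be enough to restore 85%. This softens the practical consequence, and the power actually achieved may exceed 81%. It does not repair the statement, because the calculation claims no such gain, gives no correlation and uses 0.28 as the SD of the change.

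Three further points deserve weight.

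- **Timing of dropout.** The 20% is not tied to a visit. If it describes loss over 24 weeks, loss by week 12 could be smaller and power higher. The 81% figure is the power if the full 20% is lost by week 12, and the corrected sentence should say so.
- **Which figure is wrong.** The article cannot show whether dropout, power or the total was misstated. At 80% power and 20% dropout the total would be 158 to 160, which is close to 164 but not equal to it.
- **Rounding of inputs.** If the true difference were near 0.145 and the SD near 0.275, the standardised difference would be about 0.527. The normal formula would then give 65 evaluable, and 65/0.80 = 81.25, so 82. This requires both inputs to sit at the favourable extreme of two-decimal rounding, which is unlikely.

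The size of the gap is also modest, since power stays above 80%. That bears on how much the error matters. The printed figures still disagree.

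**Conclusion.** The concern holds. On its own printed inputs the plan does not have 85% power with 164 children and 20% dropout. Power is 81.1% (t-test) or 81.7% (normal), 3 to 4 percentage points below the stated value. Meeting the stated specification would take 180 to 184 children, 16 to 20 more than planned.

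This rests on a two-sample comparison of means with SD 0.28 for the change, the full 20% lost by week 12, and no variance reduction or recovery of information from children who drop out. The match to about 10% dropout is conditional on the other inputs being as printed; it suggests where the discrepancy may have arisen but does not prove it.

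**What to change.** The sponsor should first check the original calculation and establish which figure departs from it. If 164 and 20% dropout both stand, replace the power statement with wording such as:

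> With 164 children randomised and 20% lost by week 12 (about 66 evaluable per group), power is about 81% to detect a difference of 0.14 in BMI z-score change (SD 0.28) at two-sided alpha 0.05. Power of 85% is reached if loss by week 12 is about 11% or less.

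If 10% dropout was the planning assumption, correct the dropout rate instead. If 85% is meant to rest on baseline adjustment, say so and state the assumed share of variance explained, which needs to be about 10%.

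The cost is one sentence in the protocol, and in the registry record if the same statement appears there. No further children, visits or changes to the analysis are needed. If the total and the dropout rate both stand and no gain from adjustment is claimed, the stated power becomes slightly less favourable.

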### Recruitment and informed consent

Participants will be recruited from eligible children with obesity attending non-boarding public primary schools in urban areas of Nanning. Recruitment is expected to take place from October 2025 through April 2026. All participants and their legal guardians will receive detailed information about the study procedures, potential benefits, and risks. Written informed consent will be obtained from legal guardians. In addition, assent will be obtained from children aged 8 years and older who demonstrate adequate comprehension. This study was approved by the Medical Ethics Committee of the First Affiliated Hospital of Guangxi Medical University (Approval No.: 2025-K0254).

#### Inclusion criteria

Participants meeting all of the following criteria will be included in the study:Children aged 8 to 11 years, enrolled in grades 3 through 6 of primary school, at the time of providing informed consentDiagnosed with obesity according to the diagnostic criteria outlined in the Chinese Health Industry Standard (WS/T586-2018) “Screening for Overweight and Obesity in School-age Children and Adolescents” [38].Demonstrated clear willingness from both child and parent/guardian to participate in weight management interventions.Written informed consent from the legal guardians and assent from the child participants obtained prior to enrollment.

#### Exclusion criteria

Participants meeting any of the following conditions will be excluded:Cognitive impairment or psychiatric disorders such as depression. > 5 kg weight fluctuation within 3 months prior to enrollmentCurrently enrolled in another weight-loss program or have taken medications that affect metabolism or body weight (such as glucocorticoids or antibiotics) in the past 3 months.Diagnosed with any of the following conditions: diabetes; impaired liver function or active liver disease; impaired renal function or chronic kidney disease; active malignancy or history of malignancy within the past 5 years; malabsorption, functional gastrointestinal disorders; uncontrolled hyponatremia; hyperthyroidism; hypothyroidism; Cushing’s syndrome; eating disorders such as anorexia nervosa or bulimia nervosa; or any other diseases affecting body weight.oDefinition of impaired liver function: alanine aminotransferase (ALT) and/or aspartate aminotransferase (AST) levels > 3 times the upper limit of the age- and sex-specific reference range [39].oDefinition of impaired renal function: serum creatinine levels > the upper limit of the age- and sex-specific normal range [39].History of food allergies or bariatric surgery; serious gastrointestinal disorders or gastrointestinal surgery within 12 months prior to randomization; smoking; known or suspected alcohol or recreational drug abuse; HIV infection; immunodeficiency; or any other condition that makes the participant unsuitable for the study.Any other condition deemed inappropriate by investigators

#### Withdrawal or discontinuation criteria

Participant involvement in the study will be terminated under any of the following conditions:Emergence of serious adverse events (related or unrelated to intervention) including diseases requiring excluded medications (e.g., systemic glucocorticoids), serious infectious diseases and any life-threatening conditionsParticipant or legal guardian requests to withdraw consent, or the participant is unwilling to comply with the intervention protocol, or other unforeseen reasons.

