### Quality control and data management

Data will be collected using paper Case Record Forms (CRFs). Prior to participant enrollment, all study personnel will receive standardized training to ensure proper understanding of study procedures and data recording requirements. Data will be recorded by trained investigators in real time, followed by independent double-checking by two individuals to ensure completeness and logical consistency of the forms. Data entry will be performed using a double-entry system. Upon completion, consistency checks will be conducted. Any discrepancies or abnormal values will be traced back to the original records for verification and correction. All participants will be identified using unique study codes. The linkage between personal information and study codes will be stored separately, accessible only to authorized research staff for necessary identification. All paper-based data will be securely stored in designated cabinets, with no access granted to unauthorized personnel. The hospital’s Ethics Committee will oversee the data collection and management process to ensure compliance with ethical guidelines and data protection requirements.

To promote participant retention and adherence to the follow-up schedule, regular reminders (e.g., phone calls or text messages) will be provided before each study visit. Participants and their guardians will receive educational support and periodic feedback regarding progress. Concurrent health education sessions during visits will reinforce engagement and study goal understanding. For participants who withdraw or deviate from the intervention protocol, efforts will be made to collect primary and secondary outcome data at all available time points, particularly at the 12-week and 24-week assessments.

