### Statistical analysis

Data analysis will follow the intention-to-treat (ITT) principle and will be conducted under blinded conditions. For the primary endpoint (between-group difference in BMI *z*-score change at week 12) and secondary endpoints involving continuous variables (BMI *z*-scores, waist-to-height ratios, body composition parameters, cardiometabolic markers, and psychobehavioral measures, etc.) at weeks 12 and 24, longitudinal changes will be assessed using mixed-effects models. These models will account for within-participant correlations and missing data. A time-by-group interaction term will be included to evaluate whether there are significant differences in weight reduction between the study groups. The models will be adjusted for stratification factors (age, sex, and baseline BMI *z*-score) and corresponding baseline values to control for any potential systematic group differences at baseline.

Continuous variables will be compared using independent-sample *t*-tests or Mann–Whitney *U* tests, as appropriate. Categorical outcomes, including the proportions achieving predefined reductions in %BMI95 (≥ 5%, ≥ 10%, ≥ 15%) and AE incidence, will be analyzed using chi-square tests and logistic regression. Sensitivity analyses will be conducted to test the robustness of the results. A post hoc analysis will compare adherers and non-adherers, with adherence defined as attendance at ≥ 50% of scheduled visits during the 24-week study period. Exploratory dietary adherence will be defined at the participant level as not exceeding the group-specific upper limit at ≥ 50% of available post-baseline recalls. Participants with fewer than two post-baseline recalls will be considered not classifiable for dietary adherence analyses. Statistical significance will be set at a two-tailed *P*-value of < 0.05. All analyses will be performed using SPSS and R software.

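### The withdrawal rule ends a child's study involvement for unwillingness to comply, while other sections still seek that child's outcomes, and nothing says which text governs

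*Protocol article*

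**What the plan says.** Four sections of the protocol article bear on what happens to a child who stops following the diet.

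- **Withdrawal or discontinuation criteria:** "Participant involvement in the study will be terminated under any of the following conditions". The conditions include any serious adverse event, whether or not related to the intervention, and a request to withdraw consent. As a further alternative the section lists "the participant is unwilling to comply with the intervention protocol, or other unforeseen reasons".
- **Adverse events and safety monitoring:** a child who cannot continue because of an adverse event or another unavoidable reason has the intervention discontinued. Adverse events are to be followed until they resolve.
- **Quality control and data management:** "For participants who withdraw or deviate from the intervention protocol, efforts will be made to collect primary and secondary outcome data", with weeks 12 and 24 singled out.
- **Statistical analysis:** "Data analysis will follow the intention-to-treat (ITT) principle". On the mixed-effects models: "These models will account for within-participant correlations and missing data". Also: "A post hoc analysis will compare adherers and non-adherers".

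**The concern.** The withdrawal section ends involvement in the study, not only in the diet. Because it lists withdrawal of consent separately, unwillingness to comply is enough by itself. The rule is also worded as mandatory, whereas the data management section promises only efforts. Site staff who follow the withdrawal section as written could reasonably stop measuring a child whose week-12 height and weight the primary analysis needs.

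Two things are at stake. The primary outcome could go missing because the child did not follow the assigned diet. In an open-label trial, with no stated threshold for being unwilling, that could happen at different rates in the two arms. A missing measurement also cannot be recovered at the analysis stage, however the analysis set is defined.

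**Working it through.** **1. The texts side by side**

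| Question | Withdrawal criteria | Safety monitoring | Data management | Statistical analysis |
|---|---|---|---|---|
| What ends? | Involvement in the study | The intervention | Not stated | Not stated |
| Does unwillingness to comply trigger it? | Yes | Not named | Deviators remain a source of outcome data | Non-adherers are a comparison group |
| Are outcomes still collected? | Silent | Adverse events followed to resolution | Sought, especially at weeks 12 and 24 | Needed for intention-to-treat |

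The sections can be reconciled only by assuming that ending involvement in the study still allows later study measurements. The article does not say so. The safety section blurs the distinction further, because it describes a child who cannot continue in the study and then stops only the intervention.

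**2. Effect on the planned analyses if the withdrawal rule is applied literally**

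- *Primary outcome.* The models cover weeks 12 and 24 and adjust for baseline. A child terminated before week 12 has no primary outcome. Anthropometry is also taken at weeks 4 and 8 (Intervention measures), but the article does not say whether it enters the model.
- *Dietary adherence.* Fewer than two post-baseline recalls makes a child not classifiable. Recalls are described at weeks 4, 8, 12 and 24, so a child terminated between weeks 4 and 8 would have only one.
- *Adverse events.* Incidence at weeks 12 and 24 is a secondary outcome. Ending involvement after any serious adverse event does not fit with following events to resolution.

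**3. Illustration of size**

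The document states no figure for this point, so there is none to reproduce. From Sample size estimation: planned difference 0.14, SD 0.28. Assumptions, none of them from the document: within each arm non-compliers' BMI z-score change is g = 0.28 (1 SD) worse than compliers'; all terminated children are non-compliers; none is measured later.

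- Mean change over all randomized children in an arm = compliers' mean + p × g, where p is the proportion terminated.
- Mean change over completers = compliers' mean.
- Shift in the between-arm difference = g × (p_ASER − p_control). A positive value flatters ASER.

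| Terminated, ASER v control | Shift | Share of 0.14 |
|---|---|---|
| 10% v 10% | 0.28 × 0 = 0 | 0% |
| 15% v 5% | 0.28 × 0.10 = 0.028 | 20% |
| 20% v 0% | 0.28 × 0.20 = 0.056 | 40% |
| 5% v 15% | 0.28 × (−0.10) = −0.028 | −20% |

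This is a completers' comparison, which is not the planned analysis. It shows scale only.

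**4. Precision, even when loss is equal in both arms**

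Power = Φ(0.14 / (0.28 × √(2/n)) − 1.96), where n is the number measured per group out of 82.

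- No loss, n = 82: 0.893
- 10% loss, n = 73.8: 0.859
- 20% loss (the protocol's dropout assumption), n = 65.6: 0.817
- 30% loss, n = 57.4: 0.764

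At the protocol's own dropout rate, power is already below the stated 85%. How 164 was derived is a separate question. The relevance here is only that there is no reserve to absorb avoidable missing outcomes.

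**The case against.** The strongest reply is that the data management section already settles the matter. It is the only section that addresses data collection after withdrawal. It names both those who withdraw and those who deviate, and it stresses the two key visits. On that reading the withdrawal section says when participation ends and the data management section says what is still measured. This has real force. A reader might infer from the withdrawal rule that the primary outcome will be missing in non-compliers; the document does not support that as a fact, only as a risk if the rule is taken literally. What survives is that neither section refers to the other, and the mandatory wording sits with termination.

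Other replies also stand in part:

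- *The trigger is refusal, not poor adherence.* Unwillingness most naturally means declining to go on, and the analysis plan expects non-adherers in the data. So it would be wrong to infer that the trial becomes a compliers-only comparison. The trigger still has no threshold, and refusing the diet is not the same as refusing to be measured.
- *Intention-to-treat is not contradicted outright.* It governs how randomized children are analysed, and the withdrawal rule removes nobody from the analysis set. The rule makes the principle harder to honour by losing data.
- *Missing at random may partly hold.* If the week-4 and week-8 measurements enter the model, dropout predicted by a poor observed response can be consistent with that assumption.
- *Direction is open.* Controls also receive advice on energy intake, with the same mode and frequency of supervision, and the authors expect ASER to help adherence. A bias in favour of ASER should not be inferred.
- *The article is condensed.* The full protocol may separate the two kinds of stopping. The absence of that detail is not the point; the point is that the statements printed here disagree.

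**Conclusion.** The concern holds as an unreconciled conflict within the document. One section ends study involvement for unwillingness to comply, unforeseen reasons and any serious adverse event. Others continue outcome collection, stop only the intervention, or rely on intention-to-treat, and none states precedence. The consequence is a risk of avoidable, adherence-related missing BMI z-scores at week 12, which the mixed model may not fully correct.

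The size and sign of any bias cannot be obtained from the document. The 20% and 40% figures depend on an assumed 1-SD penalty, assumed termination rates, no recovery of data and a completers' analysis that is not planned. A reader should not take them as an estimate of bias in this trial: with equal termination rates the shift is zero, and with more terminations among controls it reverses. The wording conflict is certain; the harm is conditional on how staff apply it. It should be fixed because it touches the primary endpoint and the remedy is cheap, but it does not by itself invalidate the design.

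**What to change.** Reword the withdrawal section so that it separates two events.

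1. **Discontinuing the intervention.** The clinical criteria stay with the investigators and are not touched by this point. The child remains in the study, and the existing week-12 and week-24 assessments continue to be sought, at least height, weight and adverse events, as the data management section intends.
2. **Withdrawing from the study.** Outcome follow-up ends only when consent or assent for further data collection is withdrawn. State expressly that unwillingness to comply, or another unforeseen reason, does not end it.

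Then align the withdrawal, safety and data management sections, including on what is followed after a serious adverse event, and cross-refer them so that staff have one rule.

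The cost is an amendment to the protocol and to the consent and assent wording, communicated as the Protocol amendments section provides, plus some additional measurements at visits already scheduled. The endpoint, the sample size and the analysis model do not change.
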